### Evaluation Outcomes

The primary assessment result of our study is the disparity in the TSH, T3, and T4 levels compared to the initial values. We will deem any deviation of 20% or more from the baseline as statistically significant.

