**Results:**

Any deviation of the serum TSH by more than 20% from the initial values, while keeping triiodothyronine (T_3_), and thyroxine (T_4_) levels within the normal range, will be deemed statistically significant. Consequently, we anticipate a statistically significant variation in serum TSH levels between the therapeutic enema and Kanchanar Guggul treatments. Presently, the drug preparation operations are in progress. We expect to start enrolling patients in June 2024, do data analysis in December 2025, and acquire results by early 2026, marking the end of this trial.

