### Criteria of the Assessment or Outcome Variable

A variation of more than 20% of the baseline value of serum TSH with normal values of T_3_ and T_4_ will be considered to determine the efficacy of the intervention. Therefore, decreasing serum TSH with no change in T_3_ and T_4_ means, Kshar Basti with Kanchanar Guggul is efficacious in SCH.

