### Statistical Analysis

After summarizing the data, we will use the Kolmogorov-Smirnov test to decide if the data are following a normal distribution. If normally distributed, the student *t* test will be used; otherwise, the z-test will be applied. We will use IBM SPSS (version 26) for statistical analysis. We will set the *P* value to less than .05 for statistical significance.

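### A 20% change from baseline is called statistically significant, which conflicts with the P<.05 rule and the between-arm aim, and the passages disagree on direction and on T3 and T4

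*Protocol article*

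**What the plan says.** The 20% rule appears three times in the protocol article, each time worded differently.

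- **Results, Evaluation Outcomes.** The outcome covers three analytes: "The primary assessment result of our study is the disparity in the TSH, T3, and T4 levels compared to the initial values". The rule follows: "We will deem any deviation of 20% or more from the baseline as statistically significant". It gives no direction and mentions no comparison between arms.
- **Abstract, Results.** Here the rule is for TSH only, "Any deviation of the serum TSH by more than 20% from the initial values", with T3 and T4 staying in the normal range. It too is labelled statistically significant, and the next sentence draws from it the expectation of a significant result.
- **Methods, Criteria of the Assessment or Outcome Variable.** Here it is a criterion of efficacy: "A variation of more than 20% of the baseline value of serum TSH with normal values" of T3 and T4. The following sentence adds a direction and a different condition: "decreasing serum TSH with no change in T_3_ and T_4_ means" that the treatment is efficacious.

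Other sections bear on it. Statistical Analysis names a t test (or z-test) and sets the P "value to less than .05 for statistical significance". Study Setting describes a two-arm superiority trial, and Principal Findings in the Discussion expects significance against the standard treatment. The Hypothesis is that raised TSH will decrease while T3 and T4 stay normal.

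**The concern.** Statistical significance depends on the size of a difference relative to its standard error. A fixed 20% change describes size only. Using it as the definition of significance gives the trial a second decision rule beside P<.05, and nothing says which one governs.

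The 20% rule is also a comparison with baseline. Both arms receive treatment, so both could meet it, and that would say nothing about superiority. Entry requires TSH above 4.50 µIU/mL (Diagnostic Criteria), so regression to the mean could lower TSH in either arm without any treatment effect.

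At stake is the primary conclusion. Two analysts following different sections could report opposite verdicts from the same data.

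**Working it through.** **1. Can the 20% be reproduced?** No. The protocol ties no SD, effect size or error rate to it. Sample Size Calculations gives N=40 per group and names a margin without a value. Only the sums check: 40 + 5 = 45 and 2 × 45 = 90.

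**2. Do the 20% rule and P<.05 agree?** Inputs from the protocol: n = 45 per arm, alpha .05. Assumptions: a two-sided test, and an SD of percent change that is equal in both arms (none is given).

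- Between arms: SE = SD × √(2/45) = 0.2108 × SD. A 20-point difference is significant if 20/SE exceeds t(.975, 88 df) = 1.987, that is, if SD < 20/(1.987 × 0.2108) ≈ 47.7.
- Within one arm, against baseline: SD < 20 × √45 / t(.975, 44 df) ≈ 66.6.

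| Assumed SD (points) | P for a 20-point between-arm difference | Smallest significant between-arm difference (points) |
|---|---|---|
| 20 | <.001 | 8.4 |
| 30 | .002 | 12.6 |
| 50 | .061 | 20.9 |
| 80 | .24 | 33.5 |

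At a small SD, the P<.05 rule declares significance well below 20%. At an SD above about 48 it does not declare it at 20%. The rules are not interchangeable.

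**3. Does the 20% rule address superiority?** If both arms fell by exactly 20%, both would meet the Evaluation Outcomes rule, while the between-arm difference would be zero.

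**4. The wordings side by side.**

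| Section | Direction of TSH | Role of T3 and T4 |
|---|---|---|
| Abstract, Results | either | normal range |
| Criteria of the Assessment, first sentence | either | normal values |
| Criteria of the Assessment, second sentence | fall | no change |
| Evaluation Outcomes | either | a 20% deviation itself counts |
| Hypothesis | fall | normal |

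A T3 value that moves by 20% and stays in range satisfies the normal-range condition, fails the no-change condition and counts as a significant result under Evaluation Outcomes.

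**5. How often could chance alone give a 20% fall?** Assume two log-normal TSH values with the same true level and a within-person CV that the protocol does not give. The SD of the log ratio is √(2 ln(1 + CV²)), and P(fall of at least 20%) = Φ(ln 0.8 / SD).

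| Assumed CV | One participant, fall of at least 20% |
|---|---|
| 10% | 5.7% |
| 15% | 14.5% |
| 20% | 21.3% |
| 30% | 29.5% |

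For the mean of 45 participants the SD is divided by √45. The chance of a 20% shift in either direction is then about 0.0006% at CV 20%, 0.2% at CV 30% and 1.5% at CV 40%. Regression to the mean is not modelled.

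**The case against.** The best defence is that the protocol does contain a real test and a clear intent. Statistical Analysis names a t test at P<.05, Study Setting states superiority, and the comparison with levothyroxine is repeated elsewhere. On that view the 20% is a clinical criterion, loosely labelled. This stands to the extent that a reader who infers that the trial has no valid test goes too far. It does not remove the conflict, because the Abstract and Evaluation Outcomes both use the word statistically, and the Abstract reasons from the threshold to an expected significant result.

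Three other inferences are tempting and are not supported:

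- **That a rise in TSH would count as efficacy.** The first sentence of the efficacy criterion gives no direction, but the next sentence and the Hypothesis both specify a fall. Evaluation Outcomes would call a rise significant; it does not call it efficacious. The fault is conflicting wording.
- **That noise alone could carry the trial.** The chances for single participants are sizeable, but no section says that individual deviations decide the trial. On arm means, noise rarely reaches 20%. The protocol does not state which unit the rule applies to.
- **That three primary analytes inflate the error rate to a known figure.** That needs a rule under which any one of the three suffices, and no section states one. In the Abstract and the efficacy criterion, T3 and T4 are conditions added to TSH. Multiplicity handling may also sit in an analysis plan that is not shown.

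The difference between more than 20% and 20% or more is trivial for a continuous assay and carries no weight here.

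**Conclusion.** The point holds as a conflict over the primary decision rule. The protocol defines significance in two incompatible ways, one of which is not a test and does not compare the arms. It also contradicts itself on the direction of TSH change and on the role of T3 and T4.

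The label is wrong whatever the SD. How far the two rules diverge depends on an SD of percent change that the protocol does not give: with 45 per arm and a two-sided test they coincide at about 48 points and differ on either side. If the 20% rule is read per participant, about 6% to 30% would show a 20% fall in TSH with no true change, at assumed CVs of 10% to 30%. That range is a reason not to treat an individual 20% fall as evidence of effect without comparing arms. It is not an error rate for the trial.

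**What to change.** - Delete the statistical-significance label from the 20% rule in the Abstract and in Evaluation Outcomes.
- Name one primary variable, TSH at day 181 or its change from baseline. Compare it between arms with an estimate, a 95% CI and the P<.05 test, and state whether the test is two-sided.
- Keep 20% only as a responder threshold with a direction: a TSH fall of at least 20% with T3 and T4 in the reference range, compared as proportions between arms.
- Treat T3 and T4 as supporting measures. State whether they are free or total, since Diagnostic Criteria gives ranges for the free hormones and Screening Investigations does not specify.
- Reconcile the normal-values and no-change conditions in Criteria of the Assessment or Outcome Variable.

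**Cost.** This amends the stated primary outcome, so it needs a dated protocol amendment before the data are analysed, and the registry entry (not seen here) should be checked against it. TSH, T3 and T4 are already measured on day 181, so no extra visit or sample is needed, provided that the T3 and T4 assays match the reference ranges used.

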## Discussion

### Principal Findings

The 45 participants in the control group will receive oral L-thyroxine. On the other hand, the trial group, also consisting of 45 participants, will get a treatment involving Kshar Basti and oral Kanchnar Guggul tablets. Both groups will undergo treatment for 180 days, and on day 181, we will assess the levels of TSH, T3, and T4 in the blood. We will compare the changes before and after therapy. We expect that the Ayurvedic intervention, specifically the combination of Kshar Basti and Kanchnar Guggul, will demonstrate statistically significant outcomes compared to the standard treatment. This would establish Ayurvedic intervention as a viable treatment option for SCH, eliminating the need for lifelong consumption of L-thyroxine tablets by the patient.

Hashimoto thyroiditis typically correlates with hypothyroidism. The thyroid gland produces numerous growth and vasoactive substances. The epithelial cells of the thyroid gland contain the glycoprotein known as vascular endothelial growth factor. It plays a critical role in the elevated levels of TSH in SCH.

A study compared the administration of Nigella sativa powder at a dosage of 2 grams per day for 8 weeks with the administration of placebos consisting of starches at the same dosage and duration. This RCT involved 47 human participants diagnosed with Hashimoto thyroiditis. Nigella sativa treated 23 of them, while starches served as a placebo for the remaining 24. The study determined that Nigella sativa seeds were useful in alleviating Hashimoto thyroiditis. It also successfully reduced vascular endothelial growth factor levels and body weight.

In Ayurveda, Nigella sativa is referred to as “Krishnajeeraka.” In our study, we will be administering Shivakshar Pachak Churna as “Deepan-Pachan” for the first 3 days. Nigella sativa is a constituent of Shivakshar Pachak Churna [16].

In a separate trial [17], the authors randomly assigned 53 individuals with hypothyroidism to either the treatment group or the control group, administering a placebo to the latter. The ginger group, consisting of 27 participants, was given a 500 mg capsule containing ginger twice a day, whereas the placebo group, consisting of 26 participants, was given starch. This treatment lasted for 30 days. Both groups were administered L-thyroxine. The thyroid symptoms rating questionnaire was used to evaluate the results. The initial findings of this trial showed that individuals with primary hypothyroidism who consumed ginger powder daily while receiving appropriate hormone replacement therapy (achieving biochemical euthyroid) experienced a notable decrease in symptoms associated with hypothyroidism. Our study incorporates Zanzibar as a component of the “Shivaksharpachak Churna.”

Basti therapy is recommended for the treatment of numerous physical and psychological conditions [18]. Immunomodulation was observed following Basti, according to a study that evaluated the metabolic and immunologic response to Basti therapy. One potential mechanism by which it operates is by modulating T cells, immunoglobins, and proinflammatory mediators.

A study [17] found that over 50% of people with hypothyroidism have small intestinal bacterial overgrowth (SIBO). The study found that 54% of hypothyroidism patients tested positive for SIBO using the glucose breath test, compared to 5% in the control group. Diarrhea is a common symptom among hypothyroidism patients, with a positive hydrogen breath test and antibiotic response indicating SIBO. Hypothyroidism can cause less movement in the gastrointestinal tract, leading to long-lasting gastrointestinal problems.

An additional investigation [18] demonstrated that 300 mg of Ashwagandha root extract twice daily for 8 weeks produced statistically significant outcomes. The impact of Ashwagandha root extract on the hypothalamic-pituitary-thyroid axis was hypothesized by the authors. Ashwagandha has antidopaminergic and anti-inflammatory properties. These characteristics may contribute to the thyroid-modulating effect.

Kshar Basti is a therapeutic mixture containing Tamarindus pulp, which acts as a laxative and helps alleviate gastrointestinal troubles [19]. Jaggery is beneficial for the gut microbiota [20]. It is believed that Shatavha (Anthem sowa) possesses estrogenic characteristics [21]. It affects the blood, bones, and central nervous system. The rock salt contains sodium, potassium, and chloride ions [22]. It causes the solution to become hypertonic. Guggul is derived from the latex of the Guggul plant. Recently, an article revealed the antihypothyroidism properties of the Guggul herb [23]. Therefore, the Ayurvedic treatment involving Kshar Basti and Kanchnar Guggul is believed to enhance the immune system and alleviate SCH.

The efficacy of Kshar Basti and Kanchanar Guggul in the treatment of hypothyroidism can be substantiated with dependable evidence in this study, owing to its RCT design and moderate sample size of 90. In addition, the duration of the study will be 180 days, which is sufficient to detect fluctuations in TSH and thyroid hormone levels.

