### Screening Investigations

Serum TSH will be measured before and after the study. On the 181st day, serum TSH, T_3_, and T_4_ will be measured. The above findings will be compared to the baseline findings.

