##### Course Duration

Basti will be administered daily for 8 days; after that, the participant must follow the regimen for 16 days. The total duration of the course will be 27 days (including Deepan-Pachan for 3 days), and after this course, Kanchanar Guggul will be administered for 153 days. The duration of the therapy will be 180 days, and the follow-up period will be 180 days.

Both groups of patients are restricted from taking or consuming any medications, devices, or nonpharmacological treatments that have an impact on hypothyroidism.

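### The planned t or z test does not adjust for baseline TSH, which is already collected, so precision is lost; secondarily, the lifelong L-thyroxine sentence goes further than the day-181 design

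*Protocol article*

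**What the plan says.** **Analysis.** Statistical Analysis plans a Kolmogorov-Smirnov check, then a Student t test; if normality fails, "otherwise, the z-test will be applied". Neither branch has a covariate, and the section does not name the quantity to be tested. Two other places point to change from baseline. Evaluation Outcomes gives the primary result as "the disparity in the TSH, T3, and T4 levels compared to the initial values", and Principal Findings says "We will compare the changes before and after therapy".

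**Measurements.** Screening Investigations: "Serum TSH will be measured before and after the study". Both that section and Principal Findings date the post-baseline test: "on day 181, we will assess the levels of TSH, T3, and T4 in the blood". Course Duration adds: "The duration of the therapy will be 180 days, and the follow-up period will be 180 days". The text attaches no blood test to that follow-up period.

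**Efficacy criterion.** Criteria of the Assessment or Outcome Variable uses "A variation of more than 20% of the baseline value of serum TSH" with normal T3 and T4. Diagnostic Criteria admits participants with TSH above 4.50 µIU/mL and gives no upper limit.

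**Anticipated conclusion.** Principal Findings expects a significant result against standard treatment and says this would make the Ayurvedic treatment a viable option, "eliminating the need for lifelong consumption of L-thyroxine tablets by the patient". The Conclusions section is more modest: it speaks of evidence for an option in SCH.

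**The concern.** Baseline TSH is measured in everyone and is likely to predict day-181 TSH. A t or z test on change scores subtracts it in full, which amounts to fixing its regression slope at 1. A test on day-181 values ignores it, which fixes the slope at 0. Regression estimates the slope from the data. At 45 per arm, the precision given up could decide whether a moderate effect is detected.

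The second issue is one of interpretation. Lifelong medication is the trial's stated motivation, so readers may take the sentence about eliminating it as the trial's main payoff. A TSH taken the day after treatment ends does not show what happens later, whether treatment is stopped or continued.

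**Working it through.** **Inputs from the article.** 40 + 5 = 45 per arm, and 2 × 45 = 90, as stated. The 40 cannot be rebuilt from the text at hand, and nothing below depends on it. The significance level is 0.05; I take it as two-sided. All 90 are assumed to be analysed.

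**Inputs assumed.** r is the correlation between baseline and day-181 TSH within arm: 0.3, 0.5 or 0.7. k is the day-181 SD divided by the baseline SD: 1, with 0.5 and 2 as sensitivity values. The article gives neither.

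**Variance per participant, in units of the squared baseline SD**
- Change score: k² + 1 − 2rk
- Day-181 value alone: k²
- Day-181 value adjusted for baseline: (1 − r²)k²

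Change score minus adjusted is (1 − rk)². Day-181 alone minus adjusted is r²k². Neither can be negative, so in large samples adjustment is never less precise than either simple test. It ties with change scores only when rk = 1. Estimating the slope costs a factor of about 1 + 1/86, or 1.2% in variance, and one degree of freedom.

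**Equal SDs (k = 1).** The ratio of adjusted to change-score variance is (1 + r)/2; against day-181 values alone it is 1 − r².

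| r | Reduction vs change score | Reduction vs day-181 alone |
|---|---|---|
| 0.3 | 35% | 9% |
| 0.5 | 25% | 25% |
| 0.7 | 15% | 49% |

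**95% CI half-width, 45 per arm, in SD units**
- Change score: t(0.975, 88) × √[(2/45) × 2(1 − r)] = 0.50, 0.42, 0.32
- Adjusted: t(0.975, 87) × √[(2/45)(1 − r²)(1 + 1/86)] = 0.40, 0.36 (0.365), 0.30

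**Power for an assumed true difference of 0.5 SD (noncentral t)**
- Change score: 51%, 65%, 86%
- Adjusted: 69%, 77%, 90%

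A simulation of 40,000 trials per setting agrees within a percentage point.

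**Equivalent size.** A change-score test would need about 90 ÷ [(1 + r)/2] = 138, 120 or 106 patients to match 90 with adjustment.

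**Unequal SDs.** The ratio against change scores is (1 − r²)k² / (k² + 1 − 2rk).

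| k | r = 0.3 | r = 0.5 | r = 0.7 | Reduction |
|---|---|---|---|---|
| 0.5 | 0.239 | 0.250 | 0.232 | 75% to 77% |
| 2 | 0.958 | 1.000 | 0.927 | 0% to 7% |

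**Wording of the conclusion.** Course Duration gives 3 + 8 + 16 + 153 = 180 days of therapy, so day 181 is the day after the last dose. It shows neither durability off treatment nor lifelong substitution on treatment.

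**The 20% criterion.** 4.50 ÷ 0.80 = 5.625. From any higher baseline, a fall of just 20% leaves TSH above the entry level: 6 falls to 4.8, 8 to 6.4 and 10 to 8.0.

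**The case against.** **On the test.** A randomised comparison of change scores is valid and unbiased, and covariates are often left to an analysis plan that is not shown here. Both statements stand. A reader might infer that the planned test ignores baseline or is invalid; the article does not support that, because it points to changes from baseline. What remains is an efficiency point about a test that the article does specify.

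The gain rests on correlations, SD ratios and an effect size that the article does not supply. That also stands. Entry cuts baseline TSH off at 4.50 and nothing cuts off day 181, so equal SDs are not assured. The efficacy criterion is a percentage change, which these calculations do not model.

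**On the lifelong sentence.** It is conditional, sits in the Discussion, and sets no endpoint, visit or test. It may mean replacing one therapy with another rather than stopping all treatment. This lowers its weight, but 180 days does not demonstrate lifelong substitution either. The Limitations section asks for longer follow-up only for the preventive effect.

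Two stronger readings go too far. A reader might infer that the trial takes no measurement after treatment. Figures 1 to 3 are not shown and could list later visits within the stated follow-up period, so only the text's silence can be claimed. A reader might also infer that the lifelong claim rests on the 20% criterion. It does not: the sentence depends on significance against L-thyroxine.

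**Conclusion.** The main point holds as an improvement in precision, not as an error of validity. The planned test makes less efficient use of a measurement already taken. With equal SDs and correlations of 0.3 to 0.7, adjustment removes 35% to 15% of the change-score variance. Across SD ratios of 2 to 0.5 the range is 0% to 77%, so these figures illustrate the gain and are not properties of this trial. In the worst case, where rk = 1, the loss is about 1% in variance.

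The wording point is secondary and minor. The conclusion about lifelong L-thyroxine goes beyond a design whose only dated post-baseline TSH in the text is on day 181. The 20% arithmetic shows only that meeting the efficacy criterion does not imply that SCH has resolved. How many participants that would affect is unknown, because the baseline distribution is not given.

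**What to change.** **Statistical Analysis.** Replace the t or z test with a linear regression of day-181 TSH on arm and baseline TSH, both TSH values on the log scale if skewed. Report the adjusted arm difference (a ratio if logged) with its 95% CI. Cost: one covariate that is already collected.

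**Principal Findings.** Replace the claim about lifelong L-thyroxine with wording such as: *A between-arm difference would indicate a comparative effect on TSH at day 181 in SCH; this trial does not test whether lifelong L-thyroxine can be avoided.* This agrees with the article's Conclusions section. Cost: one sentence.

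Neither change needs extra patients, visits or blood tests.
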